#### Cataract type and severity estimation

The automatic classification system will classify the cataract type (nuclear, cortical, or posterior subcapsular) and evaluate the severity.

From the acquired ultrasonic signals, several acoustic parameters in the time and frequency domains will be extracted. Then, more representative parameters will be selected through a principal component analysis and used for automatic classifier training (e.g. support vector machine, Bayes network and random forest). The performance of the different classifiers will be compared. The classification obtained by a trained specialist using the LOCS III will be used as a reference.

In the second study phase, a preliminary evaluation of the automatic classification performance will be conducted using a new dataset. It will be considered suitable if it reaches sensitivity levels higher than 90%, with a maximum significance level of 5%.

All the participants/eyes performing the ESUS study will be included in the analysis.

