**Methods:**

The pilot study protocol will be used to evaluate the feasibility and safety of the ESUS in clinical practice. The study will be conducted in subjects with age-related cataracts and on healthy subjects as controls. The procedures include data acquisition with the experimental ESUS, classification based on the Lens Opacity Classification System III (LOCS III, comparator) using a slit lamp, contrast sensitivity test, optical coherence tomography, specular microscopy and surgical parameters.

ESUS works in A-scan pulse-echo mode, with a central frequency of 20 MHz. From the collected signals, acoustic parameters will be extracted and used for automatic cataract characterization and optimal phacoemulsification energy estimation.

The study includes two phases. The data collected in the first phase (40 patients, 2 eyes per patient) will be used to train the ESUS algorithms, while the data collected in the second phase (10 patients, 2 eyes per patient) will be used to assess the classification performance. System safety will be monitored during the study.

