#### Sample size and allocation

In the first phase of the clinical study, forty participants will be included, and the two eyes will be studied. The participants will be equally distributed into four groups (based on slit lamp/LOCS III classification): participants with incipient, moderate and severe cataracts and participants without cataracts will be included as the control group. The second phase will include at least ten participants, and the two eyes will be studied. Safety will be evaluated for all the recruited participants along the first and second phases.

Since this is a protocol for a pilot study, no sample size estimate was performed. The number of eyes expected to be analysed along the study (i.e. 20 per arm) was considered adequate for this study [30]. The statistical power will be determined at the end of the study for statistically significant results.

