### Statistical analysis

#### Feasibility assessment

The feasibility of the ESUS technique will be evaluated based on cataract detectability, cataract classification and OPE estimative performances and on the ESUS safety.

Cataract detectability will be considered suitable if at least 90% of the cases detected through slit lamp observations are identified by the ESUS.

The cataracts classification will be considered suitable if sensitivity levels higher than 90 %, with a maximum significance level of 5%, are reached.

The system efficacy for the OPE will be considered suitable if the prediction accuracy is higher than 90%.

Since the clinical procedure involved in data acquisition with the ESUS is similar to the used in biometry for IOL power calculation, the procedure viability is not object of the study.

The ESUS safety will be considered suitable under two conditions: (i) there are no occurrence of serious adverse event associated with ESUS whose causes cannot be rectified; (ii) the occurrence rate of mild to moderate ESUS-related adverse events is lower than 5%.

The feasibility study will be considered successful if at least the primary objective, detection of the presence of cataracts, and the secondary objective of cataracts classification (type and severity) are reached and if the safety of the ESUS technique is verified.

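### At the planned second-phase size of 10 participants (20 eyes), a test that classification sensitivity exceeds 90% at the 5% level cannot succeed even with every eye correct

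*Protocol article*

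**What the plan says.** The classification criterion appears twice in the protocol article. Under Feasibility assessment: "The cataracts classification will be considered suitable if sensitivity levels higher than 90 %, with a maximum significance level of 5%, are reached". Under Cataract type and severity estimation, where it is tied to the second phase: "It will be considered suitable if it reaches sensitivity levels higher than 90%, with a maximum significance level of 5" per cent.

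The data for that judgement are separate from the training data: "In the second study phase, a preliminary evaluation of the automatic classification performance will be conducted using a new dataset". The abstract gives their size: "the second phase (10 patients, 2 eyes per patient) will be used to assess the classification performance". The section Sample size and allocation words it as a minimum: "The second phase will include at least ten participants, and the two eyes will be studied". The same section adds: "Since this is a protocol for a pilot study, no sample size estimate was performed".

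The criterion is binding. Under Feasibility assessment: "The feasibility study will be considered successful if at least the primary objective, detection of the presence of cataracts, and the secondary objective" of classifying type and severity are both met, and if safety is shown as well.

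The neighbouring criteria have a different form. Detection needs at least 90% of slit-lamp cases, and the energy estimate needs accuracy above 90%. Neither carries a significance level.

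**The concern.** A threshold of 90% joined to a 5% significance level reads most naturally as a demand to show, at that level, that true sensitivity is above 90%. Such a demand has a smallest workable sample, because even an error-free result carries limited information. Twenty eyes fall below it.

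Two things are at stake. If the rule is applied as a test against 90% with 10 participants, no result could satisfy it, and overall success would be lost with it. If it is applied loosely, a result such as 19 of 20 could be reported as meeting a 5% significance criterion although its exact 95% interval runs from 75.1% to 99.9%. The results are meant to support a larger study, so either outcome would mislead that decision.

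**Working it through.** **Inputs**
- Threshold 90% and level 5%: Feasibility assessment; Cataract type and severity estimation.
- Second phase: 10 participants × 2 eyes = 20 eyes (abstract; a minimum in Sample size and allocation).
- First phase: 40 participants × 2 eyes = 80 eyes, used for training.
- Assumption: the null hypothesis is sensitivity ≤ 90%. The article does not name it.
- Assumption most favourable to the plan: all 20 eyes have cataract and are independent.

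**The plan's own figure.** 80 eyes / 4 groups = 20 eyes per arm, as stated. This describes the first phase and is not a calculation for the classification rule.

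**Best possible result, 20/20, tested against 90%.** With every eye correct, the exact one-sided p-value is 0.9^n.
- 0.9^20 = 0.122, above 0.05.
- Exact lower limit, one-sided 95%: 0.05^(1/20) = 0.861.
- Exact lower limit, two-sided 95%: 0.025^(1/20) = 0.832.

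Other methods at 20/20: score test p = 0.068; mid-p = 0.061; Wilson lower limit 0.881 one-sided and 0.839 two-sided. All fail. The one-sided Jeffreys limit is 0.9095 and would pass; the two-sided Jeffreys limit is 0.883 and would not.

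**Smallest error-free sample that passes the exact test**
- One-sided 5%: 0.9^28 = 0.0523 fails and 0.9^29 = 0.0471 passes, so 29 cataract eyes.
- One-sided 2.5%: 36 cataract eyes (0.9^36 = 0.0225).
- With one error allowed: 46 and 54 eyes respectively.

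**Less favourable conditions**
- If 5 of the 20 eyes are controls, 15 cataract eyes remain: 0.9^15 = 0.206.
- The correlation between fellow eyes is not given. If the eyes are independent, p = 0.122. If the two eyes of a participant always agree, the information is that of 10 eyes: 0.9^10 = 0.349. The truth lies in that range.

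**Alternative reading: observed value above 90% plus a test against chance**
- 18/20 = 90% is not above 90%, so 19/20 is needed.
- 19/20 against 50%: (20 + 1)/2^20 = 0.00002.
- Any result that clears the observed threshold is therefore far below 5% against chance, and the clause never decides anything.

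**How an observed-proportion rule would behave at 20 independent cataract eyes (at least 19 correct)**

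| True sensitivity | Chance of passing |
|---|---|
| 95% | 0.736 |
| 90% | 0.392 |
| 85% | 0.176 |

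**The case against.** A reader might infer that the trial must fail whatever the device does, or that success is unreachable at any size the text allows. The documents do not support that, for two reasons.

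First, ten is a minimum in the sample size section; only the abstract gives a flat 10. With 15 participants and cataract in both eyes, 30/30 gives 0.9^30 = 0.042 and passes the one-sided test. This stands. But ten is the only number offered, no calculation points to a larger one, and 30/30 would occur only 21.5% of the time with a true sensitivity of 95% (54.5% with 98%).

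Second, the article does not say that the 5% level tests sensitivity against 90%. Under a test against chance the criterion can be met, and the clause is redundant rather than impossible. This also stands. It changes the nature of the fault without removing it.

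It can also be said that a pilot needs no power calculation, and that the choice of test, its sidedness and the handling of paired eyes may sit in a fuller document. Both are fair, and no weight is placed on their absence here. The point rests on what the article itself fixes: the threshold, the level, the evaluation data set and its planned size. A fuller document could name a test, but an exact test against 90% would still fail at 20/20.

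**Conclusion.** The concern holds at the planned size. With 10 participants and 20 eyes, a test of sensitivity above 90% at the 5% level fails even with no misclassification: p = 0.122, with a shortfall of at least 9 cataract eyes (29 − 20) at one-sided 5% and 16 (36 − 20) at one-sided 2.5%. Control eyes, any error and fellow-eye correlation widen the gap.

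The conclusion assumes a null of 90% and an exact, score, mid-p or Wilson method; a one-sided Jeffreys limit would pass at 20/20. Under a null of chance, the 5% clause has no effect. Neither reading gives a workable use of the significance level at the planned size, and the criterion governs overall success, so the wording should be corrected before second-phase data are assessed.

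**What to change.** Delete the significance-level clause from both sections where it appears. Restate the second-phase rule in the same form as the detection and energy criteria, for example: *Classification is suitable if more than 90% of second-phase cataract eyes are classified correctly against LOCS III. The proportion is reported with a 95% confidence interval, exact or allowing for two eyes per participant, and is descriptive.* If all 20 eyes have cataract, this means at least 19 correct; with 15 cataract eyes it means at least 14 (14/15 = 93.3%; 13/15 = 86.7%).

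Do not enlarge the test set with first-phase training eyes. Several classifiers are compared and features are selected on those data, so their results would risk being optimistic, and the plan's independent evaluation would be lost.

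The cost is two sentences of wording and no added patients. The claim becomes less favourable: an observed proportion with a wide interval instead of a significance statement.

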#### OPE estimation

To develop an OPE estimator, the acoustic parameters extracted from the ultrasonic signals in the first phase will be correlated with the maximum energy used in the phacoemulsification surgery for each participant eye. Only surgeries without surgical or postoperative complications will be considered. A confidence interval of 95% followed by multiple comparison correction will be used to assess the significance of the correlations.

In the second phase, the acoustic parameters extracted from the ultrasonic signals will be used to predict the safety and risk intervals of phacoemulsification energy based on the correlation curves. To evaluate the prediction accuracy, surgeons should initiate surgeries at minimum energy levels and increase them gradually until they reach an efficient energy level. Then, the maximum energy level applied during surgery and the occurrence of surgical and/or postoperative complications will be compared with the safe and risk energy intervals predicted with the correlation curves. The system efficacy will be considered suitable if the prediction accuracy is higher than 90%.

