#### Timelines and methods for outcomes recording

Study status: not yet recruiting

Starting date: October 2022

The total duration of the clinical study will be 15 months, and it will be divided into two phases:First phase: 9 months (6 months for recruitment and 3 months for participant follow-up).Second phase: 6 months (3 months for recruitment and 3 months for participant follow-up).

In the first phase, the cataract type and severity measured with slit lamp/LOCS III and contrast sensitivity will be used to train the algorithms for cataract detection and classification in humans. The surgical records (maximum phacoemulsification energy, phacoemulsification time and surgical complications), number and morphology of endothelial cells (measured by specular microscopy), the presence of macular oedema (assessed by OCT) and postoperative complications will support algorithm development for the estimation of OPE.

In the second phase, the cataract type and severity classification and OPE estimation will be implemented with the ESUS using the algorithms developed/trained in the first phase. The remaining study assessments will be used for preliminary performance evaluations. The methods for algorithm development are described in the “Statistical analysis” section.

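### The energy (OPE) curves are fitted only to complication-free surgeries, so their 'risk interval' does not estimate complication risk, and a model with no information can meet the accuracy rule of more than 90% when complications are rare

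*Protocol article*

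**What the plan says.** The OPE estimation section of the protocol article describes development and testing.

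- **Development (phase 1).** The acoustic parameters "will be correlated with the maximum energy used in the phacoemulsification surgery for each participant eye". Eyes are then restricted: "Only surgeries without surgical or postoperative complications will be considered".
- **Prediction (phase 2).** The acoustic parameters "will be used to predict the safety and risk intervals of phacoemulsification energy based on the correlation curves".
- **Test (phase 2).** The maximum energy applied, together with any surgical or postoperative complication, "will be compared with the safe and risk energy intervals predicted with the correlation curves". Surgeons are to start at the lowest level and step up.
- **Pass mark.** "The system efficacy will be considered suitable if the prediction accuracy is higher than 90" per cent. The Feasibility assessment section repeats this threshold. Neither section says what counts as a correct prediction.

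Three other sections bear on this:

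- Timelines and methods for outcomes recording says that surgical records, endothelial cell findings, macular oedema and postoperative complications will support development of the OPE algorithm.
- Phacoemulsification surgery says that operations follow normal practice and that the study does not interfere with them.
- Feasibility assessment makes overall success depend on detection, classification and safety. The OPE criterion is not on that list.

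**The concern.** There are two separate problems.

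**What the curves can show.** A curve of energy used against acoustic parameters, fitted after removing every complicated eye, describes the energy surgeons used when nothing went wrong. It holds no information on how the chance of harm changes with energy. Absence of a complication also does not make an energy optimal. The Specular microscopy section links endothelial cell loss to excessive energy, and an eye given more energy than it needed, but with no recorded complication, enters the fit as a valid value.

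**What the pass mark can show.** The test combines two outcomes, applied energy and complications, in one accuracy figure. It neither requires risk to be recognised nor compares the result with an uninformative predictor. When complications are rare, high accuracy can come from their rarity alone.

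The stake is how an OPE result would be used. OPE estimation is in the article's title and is secondary objective iii, and the Discussion ties it to fewer complications and shorter surgery. A pass could be carried into the larger study as evidence that ultrasound can guide energy.

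**Working it through.** **The plan's own figure.** Sample size and allocation: "In the first phase of the clinical study, forty participants will be included, and the two eyes will be studied", in four equal groups. 40 × 2 / 4 = 20 eyes per arm, which reproduces the stated 20.

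**Operated eyes.**

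- Phase 1: three of the four groups have cataract, so at most 30 × 2 = 60 eyes are operated. If only one eye per patient is operated, the number is 30.
- Phase 2: at the stated minimum of ten participants, at most 10 × 2 = 20 eyes. Second-eye surgical data are conditional on an indication (Participation time and anticipated withdrawal; Table 1, note c), so 10 eyes are shown as well.

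**Complication rate.** The Background figure of 5 to 10% is worded as a share of postoperative complications, not a rate per surgery. The per-eye rate is therefore assumed: 2%, 5% and 10%, with 20% as a high case.

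**Step 1: events in development.** From 60 operated eyes the rule drops 60 × 0.02 = 1.2, 60 × 0.05 = 3 or 60 × 0.10 = 6 complicated eyes in expectation. The number left in the fit is 0 by rule, so the probability of a complication given energy and acoustic parameters cannot be estimated from it.

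**Step 2: a rule that always says safe.** Suppose accuracy means agreement between the predicted interval and complication status, with independent eyes. More than 90% of 20 eyes means at least 19 correct, so P(pass) = (1 − p)^20 + 20p(1 − p)^19. At p = 0.05 this is 0.358 + 0.377 = 0.736. More than 90% of 10 eyes means all 10 correct, so P(pass) = (1 − p)^10.

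| Assumed rate p | 20 operated eyes | 10 operated eyes |
|---|---|---|
| 2% | 0.940 | 0.817 |
| 5% | 0.736 | 0.599 |
| 10% | 0.392 | 0.349 |
| 20% | 0.069 | 0.107 |

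The chance of no complication at all in 20 eyes, which leaves the risk side untested, is (1 − p)^20 = 0.67, 0.36 and 0.12 at 2%, 5% and 10%.

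**Step 3: a fitted curve with no signal.** This is closer to the described procedure. A simulation (8,000 runs) used 60 operated phase 1 eyes with the complicated ones dropped, zero correlation between acoustic parameter and energy, and complications independent of energy. A 95% prediction band served as the safe interval, and there were 20 phase 2 eyes.

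| Assumed rate | Two-sided band: mean accuracy; P(pass) | Upper limit only: mean accuracy; P(pass) |
|---|---|---|
| 2% | 0.931; 0.602 | 0.955; 0.772 |
| 5% | 0.906; 0.436 | 0.929; 0.582 |
| 10% | 0.857; 0.204 | 0.881; 0.301 |

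Hand check at 2%, two-sided: 0.95 × 0.98 + 0.05 × 0.02 = 0.932, against 0.931 simulated.

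**The case against.** **The always-safe rule is not the planned procedure.** The plan derives intervals from fitted curves and also compares applied energy with them, so a prediction can fail on energy alone. This stands. The step 2 figures depend on one reading of accuracy, and step 3 is the fairer guide. Step 3 gives lower pass probabilities, but still substantial ones for a model with no information.

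**Twenty operated eyes is not stated.** Correct: both eyes are studied, but not necessarily operated, and the make-up of phase 2 is not given. Hence the 10-eye column.

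**The complication rate could exceed 10%.** If detected endothelial cell loss counts as a complication, the rate could be higher, and at 20% the always-safe rule usually fails. On that reading the exclusion would also remove some over-treated eyes. This limits the size of the second problem but leaves the first untouched.

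**A limit can be drawn above the range of uncomplicated surgeries.** It can, and it would be a legitimate reference limit. It marks unusual energy, however, and is not a limit estimated from harm.

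**The Timelines section need not conflict with OPE estimation.** Using endothelial and OCT findings to decide which eyes are uncomplicated is a form of support. That is a possible reading, so the two sections need aligning rather than being plainly contradictory.

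**The full protocol may define accuracy.** It may, and the missing definition alone is not the point. The stated rule, to fit complication-free eyes and read risk from the result, is the problem whatever the definition.

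**Conclusion.** The concern holds in a limited form. As written, the risk interval is a statement about usual energy in uncomplicated eyes and not an estimate of complication risk. This needs no assumed rate. The pass mark also fails to separate an informative model from an uninformative one when complications are rare: the zero-correlation curve passes about 0.60–0.77 of the time at 2%, 0.44–0.58 at 5% and 0.20–0.30 at 10%. These figures rest on the assumed rates, independent eyes, 20 operated phase 2 eyes and scoring against complication status.

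A reader might infer that a pass is close to certain, taking 0.94 as the expected figure. The documents do not support that: it is the most favourable of the 2%, 5% and 10% cases, and at 10% both uninformative predictors usually fail in 20 eyes. A reader might also infer that the study's overall conclusion is at risk. It is not, because the Feasibility assessment section does not require the OPE criterion for success. The damage is confined to secondary objective iii and to any claim built on it.

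**What to change.** 1. **Interval.** Rename the risk interval as a reference range of energy in uncomplicated surgeries. Alternatively, keep all operated phase 1 eyes and relate the continuous change in endothelial cells to energy and acoustic parameters. Specular microscopy is already scheduled before surgery and one week after it. Do not fit a complication model: about 1 to 6 events in at most 60 eyes cannot support one.
2. **Pass criterion.** Replace accuracy above 90% by the error between predicted and applied maximum energy: mean absolute error, limits of agreement and interval width. Require improvement over a reference that uses LOCS III grade alone or the phase 1 mean. Do not use interval coverage as the criterion, because a 95% prediction interval covers about 95% of eyes even with no acoustic signal.
3. **Complications.** Report them separately as counts, with the number of operated eyes.
4. **Reconcile.** Align Timelines and methods for outcomes recording with OPE estimation on how endothelial, OCT and complication data enter development. Align Phacoemulsification surgery with OPE estimation on how phase 2 operations are conducted.

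The cost is a change of wording and modest extra modelling on data already planned, in a study the article describes as not yet recruiting. The OPE claim becomes more modest.

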### Outcomes

#### Primary outcome

The presence of cataract is obtained with the ESUS.

Secondary outcomes are as follows:i.Cataract type and severity estimated with ESUS based on the LOCS IIIii.Cataract hardness estimated with ESUS, measured in GPaiii.OPE level estimated with ESUS based on the parameters indicated by the phacoemulsifieriv.Number and severity of ESUS-related adverse events

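### The OPE outcome is an estimated energy level, but its over-90% rule scores agreement with predicted intervals of unlimited width, so a moderate acoustic signal may pass as often as a strong one

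*Protocol article*

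**What the plan says.** All references are to the protocol article.

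- **Outcomes** lists secondary outcome iii as "OPE level estimated with ESUS based on the parameters indicated by the" phacoemulsifier: one energy level per eye.
- **OPE estimation, phase 1**: acoustic parameters are correlated with the maximum energy used at surgery. On which eyes enter: "Only surgeries without surgical or postoperative complications will be considered". On testing: "A confidence interval of 95% followed by multiple comparison correction will be used to assess the significance of the correlations".
- **OPE estimation, phase 2**: the parameters "will be used to predict the safety and risk intervals of phacoemulsification energy based on the correlation curves". The maximum energy applied and any surgical or postoperative complications "will be compared with the safe and risk energy intervals predicted with the correlation curves".
- **Threshold**: "The system efficacy will be considered suitable if the prediction accuracy is higher than 90" per cent. Feasibility assessment repeats it: "The system efficacy for the OPE will be considered suitable if the prediction accuracy is higher than 90" per cent.
- **Feasibility assessment** bases overall success on detection, classification and safety. OPE is not among the required elements.

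The article gives no width or coverage level for the intervals, no definition of a correct prediction and no maximum error. It does not say whether a non-significant correlation is dropped before phase 2.

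**The concern.** The outcome is a level, and the rule scores membership of an interval. These measure different things. How good an estimated level is depends on how far it lies from the energy actually needed. Agreement with an interval depends also on how wide the interval is, and a wider safe interval is easier for an uncomplicated eye to satisfy. If the width follows the scatter around the fitted curve, a poorer signal produces a wider interval and leaves the agreement rate where it was.

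At stake is the separate statement that ESUS is suitable for OPE estimation. That statement supports the surgical-planning claim in the abstract, introduction and discussion, and it would feed the larger study. It could be made when eyes receive broad and nearly identical ranges, which would say little about the individual patient.

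**Working it through.** **The plan's own figure.** Sample size and allocation expects 20 eyes per arm: 40 participants / 4 groups x 2 eyes = 20. This reproduces. It is the only size figure; no operating characteristic is stated for the OPE rule.

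**Inputs from the article.**
- Phase 1: "forty participants will be included, and the two eyes will be studied", in four equal groups of which three have cataract. At most 3 x 10 x 2 = 60 operated eyes, fewer after complicated surgeries are removed.
- Phase 2: at least 10 participants, so 20 operated eyes if all have bilateral surgery. Participation time and anticipated withdrawal makes second-eye surgery conditional on indication, so 15 and 10 eyes were also examined.
- Pass: more than 90%, which means at least 19 of 20, 14 of 15 or 10 of 10.

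**Assumptions, not in the article.** One acoustic parameter, linear fit, normal errors, uncomplicated eyes, independent eyes unless stated, and energies arising in the same way in both phases. The main interval is a 95% prediction interval with half-width

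t(0.975, n1 - 2) x s x sqrt(1 + 1/n1 + (x - mean x)^2 / Sxx),

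where s estimates SD x sqrt(1 - rho^2). A weaker correlation rho raises s and widens the interval; coverage stays at 95%.

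**Exact check at 95% coverage, whatever the correlation.**
- n = 20: 0.95^20 + 20 x 0.05 x 0.95^19 = 0.358 + 0.377 = 0.736 (before rounding of terms)
- n = 15: 0.95^15 + 15 x 0.05 x 0.95^14 = 0.463 + 0.366 = 0.829
- n = 10: 0.95^10 = 0.599

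**Simulation, 60 training and 20 test eyes, 8,000 runs per row.** Columns 2 and 4 to 6 are pass probabilities. A screen means that the correlation must first be significant in phase 1; the 0.05/10 level assumes ten parameters.

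| rho | 95% interval, no screen | Mean width (SD of energy) | Screen at 0.05 | Screen at 0.05/10 | Error limit fixed at 1 SD either way |
|---|---|---|---|---|---|
| 0 | 0.739 | 4.05 | 0.032 | 0.004 | 0.004 |
| 0.3 | 0.735 | 3.86 | 0.472 | 0.221 | 0.006 |
| 0.6 | 0.729 | 3.24 | 0.729 | 0.725 | 0.044 |
| 0.9 | 0.739 | 1.77 | 0.739 | 0.739 | 0.912 |

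The Monte Carlo standard error near 0.74 is sqrt(0.74 x 0.26 / 8000) = 0.005, so column 2 is flat. The widths follow sqrt(1 - rho^2): 3.24/4.05 = 0.80 at rho 0.6, and 1.77/4.05 = 0.44 at rho 0.9. At rho 0.6 the interval is only 20% narrower than with no signal.

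**Sensitivity without a screen.** The pass probability stays flat in rho for:
- 90% intervals (0.41 to 0.42)
- one-sided 95% limits (0.73 to 0.74)
- 15 test eyes (0.82 to 0.83)
- 30 training and 10 test eyes (0.62 to 0.63)
- a within-patient correlation of 0.5 (0.715 at rho 0, 0.714 at rho 0.9)

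**Sensitivity with a screen at 0.05.** At rho 0 the pass probability is 0.037 with 15 test eyes, 0.020 with 30 training and 10 test eyes, and 0.045 with a within-patient correlation of 0.5.

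**The level itself does discriminate.** With 30 training and 15 test eyes, the root mean squared error of the estimated level is 1.04, 0.95 and 0.62 SD of energy at rho 0, 0.4 and 0.8. The last column of the table shows the same thing as a pass rule.

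**The case against.** **The significance test may be a screen.** The phase 1 test stands in the same section, and it is natural to read it as deciding which correlations go forward. The interim analysis between phases would also show a null result. A reader might infer that a signal unrelated to energy passes as often as a strong one. The documents do not support that as a general statement: it needs the test not to act as a screen, and the article says neither that it does nor that it does not. With a screen, rho 0 passes in about 3% of studies, and rho 0.3 falls to 47% or 22%. The screen does not separate rho 0.6 from 0.9, because significance is not precision.

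**The interval type is assumed.** This is correct. If the full protocol fixes the width independently of the fit, the flat result disappears, as the last column of the table shows. A condensed article may leave the construction out, and its absence is not the point here. The point is that the stated rule scores a different quantity from the stated outcome. Scaling to residual spread is a plausible reading, because curves fitted only to complication-free surgeries offer no contrast from which to set a risk boundary.

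**Complications also count.** A safe interval wide enough to cover everything would be wrong for an eye with complications, so width is not wholly free. This stands. Its size is unknown, because complications were not modelled.

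**The level may still be compared.** Timelines and methods for outcomes recording says that the remaining assessments will serve performance evaluation, and these include recorded energy. So it cannot be said that the comparison will never be made, only that no stated criterion uses it.

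**The energies may arise differently.** Phacoemulsification surgery describes normal practice without interference from the study, while OPE estimation describes a gradual increase from minimum energy when phase 2 accuracy is assessed. If the two differ, nominal coverage is not assured. This stands, and it bears on the fix as well.

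**Conclusion.** The concern holds in a limited form. The outcome is an estimated level; the over-90% rule scores agreement of maximum energy and complications with intervals that have no width limit and no no-signal comparator. For intervals scaled to the phase 1 residual spread, the rule by itself does not respond to the strength of the signal: about 0.74 with 20 eyes, 0.83 with 15 and 0.60 with 10 by exact binomial. With or without a phase 1 screen at 0.05, rho 0.6 and 0.9 pass about equally often with 60 training and 20 test eyes (0.729 and 0.739), with intervals that differ in width by a factor of 3.24/1.77 = 1.8.

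For an unrelated signal the answer depends on an unstated step: about 0.74 without a screen, about 3% with one. These figures rest on the assumed interval, a single parameter, uncomplicated eyes and the same energy process in both phases.

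The consequence is confined to the OPE suitability verdict. Overall success does not require OPE, and this is a first-in-human pilot.

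**What to change.** In Feasibility assessment and OPE estimation:

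1. For each operated phase 2 eye, compare the ESUS-estimated OPE level with the recorded maximum energy.
2. Define accuracy as the share of eyes whose error lies within a margin fixed before phase 2. The 1 SD limit above is only an illustration.
3. Also require a lower mean absolute error than a reference that gives every eye the phase 1 mean energy. Both conditions are needed, because with no signal the fitted line and the mean perform almost alike and the benchmark alone can be met by chance.
4. Report interval coverage only together with interval width.
5. State whether only significant correlations are carried forward.
6. Reconcile the two descriptions of how surgical energy arises (Phacoemulsification surgery and OPE estimation). A phase 1 level and a phase 1 mean are both being compared with phase 2 energies.

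The cost is wording plus a short analysis of data already collected. The downside is that a margin must be agreed in advance and the result may look less favourable than interval agreement.
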